### Dietary assessment

Dietary assessment will be collected by asking study participants to complete the DHQ-III survey at months 0, 3, 12, and 24. Additionally, participants randomized to the MPE or TROO ketogenic diets will be instructed to record key study diet components each day using a study specific three-item questionnaire in the study-related (MyCap) application on their smart device. To decrease participant burden, completing MyCap is optional. The Healthy Eating Index (HEI), which is designed to determine how closely dietary intake mirrors the DGA, will be applied to the usual care control group to determine adherence to the DGA.

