### Eligibility criteria {10}

The inclusion criteria include:A definitive diagnosis of RRMS based on the 2017 revised McDonald Criteria [28].The ability to prepare, or availability of another person to prepare, home-cooked meals.Must own a computer, smartphone, or tablet device with internet access to complete online surveys and capable of running study-related applications.Must reliably attend scheduled visits with the study team (including virtual and site visits) and follow study procedures.Be between the ages of 18 and 70 at the time of consent.Must be able to walk 25 feet without support OR with only unilateral support from a cane or walking stick (ankle/foot orthotic is allowed).Willingness to be randomized and follow any of the study diets.Must consent to sharing the clinical notes from their primary care and neurology providers during the study period.Must live or reside in North American countries (United States, Canada, or Mexico).

The exclusion criteria include:Moderate or severe cognitive impairment, as assessed by Short Portable Mental Status Questionnaire (SPMSQ), and defined as more than four errors.Use of insulin, warfarin, or weight loss medications such as orlistat that cause fat malabsorption.Worsening of symptoms resulting in the initiation or change of treatment including steroids (e.g., solumedrol, prednisone) or DMTs within 4 weeks prior to consent.Treatment for cancer by radiation or chemotherapy within 12 months prior to consent, other than skin cancer.Diagnosis of clinically significant heart disease, liver disease, kidney disease, or history of oxalate kidney stones.Diagnosis of type II diabetes that does not have approval from treating physicians to adopt any of the three study diets.Clinical diagnosis of a psychiatric condition that may impact study adherence (e.g., schizophrenia, bi-polar disorder, severe depression and/or anxiety).An active eating disorder such as anorexia, bulimia, binge eating, or orthorexia.Measurement of Body Mass Index (BMI) < 20.Confirmation of pregnancy or planning to become pregnant within the next 2 years.History of diagnosed fat intolerance/malabsorption such as cholecystectomy or uncontrolled exocrine pancreatic insufficiency.Participation in another research study investigating MS treatments, diet, or exercise.Presence of a contraindication to completing a brain MRI or having claustrophobia which interferes with completion of MRI studies without the use of sedation.

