## Interventions

### Explanation for the choice of comparators {6b}

Since nutrition counseling is not a current clinical recommendation for individuals with MS, the usual care control group will not receive diet education from the study RDN. Instead, they will receive educational materials and resources from the 2020–2025 DGA and be allowed to utilize the resources to any degree of compliance. The rationale for providing only educational materials on the DGA to the usual care control group is that: 1) nutrition counseling and education provided by RDNs is not part of the standard of care for MS in the U.S. and 2) that people with MS are recommended to follow a general healthy diet such as the DGA. Giving study participants educational material on the DGAs and the choice to follow the DGA recommendations to any degree of compliance maintains clinical equipoise of the usual care control.

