### Methods in analysis to handle protocol non-adherence and any statistical methods to handle missing data {20c}

A sensitivity analysis including only participants who were adherent to their assigned study diet will be conducted. Participants in the MPE diet group will be included in the sensitivity analysis if DHQ-III survey indicate that they consumed within 20% of recommendations for key intervention diet components (≥ 5 cup equivalent servings of total fruit and vegetables). TROO ketogenic participants will be included in the sensitivity analysis if they achieved a ketogenic ratio (KR) value of > 1.5 on DHQ-III surveys or if they are determined to be in nutritional ketosis in 80% of the ketone readings throughout the trial. KR value ≥ 1.5 is considered the minimum threshold to predict a ketogenic diet and will be calculated as follows: (0.9*grams fat + 0.46*grams protein) divided by (0.1*grams fat + 0.58*grams protein + grams total carbohydrate – grams total fiber). Control participants will be excluded from the sensitivity analysis if they have a significant change in HEI 2020 scores, defined as 10 points or more in either direction from baseline values. In all analyses, missing data will be modeled within the GLMM framework, which provides better power and reduced bias compared to other methods to handle missing data.

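### The adherent-only analysis screens controls by HEI change alone, which cannot identify controls who take up a study diet after randomization

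*Protocol article*

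**What the plan says.** Under Dietary assessment, the article plans "asking study participants to complete the DHQ-III survey at months 0, 3, 12, and 24", with no restriction by arm. It describes HEI as an index of how closely intake follows the DGA and says that it "will be applied to the usual care control group to determine adherence to the DGA".

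The section on non-adherence and missing data {20c} then sets one rule per arm for an analysis restricted to adherent participants:

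- MPE: "Participants in the MPE diet group will be included in the sensitivity analysis if DHQ-III survey indicate that they consumed within 20% of recommendations". The named component is fruit and vegetables, at five cup equivalents or more.
- TROO: "TROO ketogenic participants will be included in the sensitivity analysis if they achieved a ketogenic ratio (KR) value of > 1.5 on DHQ-III surveys". The alternative route is nutritional ketosis in 80% of ketone readings.
- Control: "Control participants will be excluded from the sensitivity analysis if they have a significant change in HEI 2020 scores". The size of change that counts is "defined as 10 points or more in either direction from baseline values".

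The section on improving adherence {11c} gives the same MPE and TROO criteria. The section on the choice of comparators {6b} says that controls receive DGA materials and will "be allowed to utilize the resources to any degree of compliance". The inclusion criteria require "Willingness to be randomized and follow any of the study diets".

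**The concern.** The control rule is meant to give a clean comparator, but it uses a yardstick that points at the DGA and not at either study diet. It can err in two ways. A control who moves to a study diet while the HEI total moves by fewer than 10 points is retained as adherent. A control whose HEI moves further is removed, but the rule does not say why: that person may have switched to a study diet or may simply have used the DGA materials as allowed.

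Uptake in the control arm is foreseeable. Controls entered willing to follow any of the diets, learn their assignment at the baseline visit and are followed for 24 months. The Background says that up to half of people with MS report changing their diet. The point concerns change after randomization, not diets already followed at entry.

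What is at stake is interpretation. If QoL does not differ, readers will ask whether the arms separated in what they ate. If it does differ, they will ask whether intake differed in the intended way. No stated measure is scored in all three arms to answer either question.

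**Working it through.** **The plan's own sample size.** 36 / (1 − 0.33) = 53.7, rounded up to 54 per group; 54 × 3 = 162. Both stated figures reproduce. The 36 itself cannot be rebuilt, because the contents of Table 4 are not available here.

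**Which measure is applied where** (Dietary assessment, {11c}, {20c}, Ketone monitoring, blood measurements):

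| Measure | Data available in | Stated rule applies to |
|---|---|---|
| HEI (DHQ-III) | all arms | control |
| Ketogenic ratio (DHQ-III) | all arms | TROO |
| Fruit and vegetable cups (DHQ-III) | all arms | MPE |
| Home ketone readings | TROO | TROO |
| Laboratory β-hydroxybutyrate, months 0 and 24 | all arms | none (listed under nutritional safety) |

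The ketogenic ratio needs only grams of fat, protein, carbohydrate and fiber. It can therefore be computed for a control exactly as for a TROO participant.

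**What the MPE criterion can detect.** If 20% is read as a shortfall allowance, the threshold is 0.8 × 5 = 4 cup equivalents of fruit and vegetables. A control could reach that without eliminating any food. Applying the MPE criterion to controls would therefore not identify MPE uptake; intake of the eliminated food groups is needed.

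**Size in the analysis concerned.** Let c be the share of controls who switch, and h the share of switchers whose HEI moves by 10 points or more. If no other control is removed, the share of switchers among the controls retained is

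c(1 − h) / (1 − ch).

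At h = 1 this is 0; at h = 0 it is c. With c assumed at 10% or 20%, the retained share lies between 0 and 10%, or between 0 and 20%. The documents give neither c nor h.

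**What uptake would do to the main contrast (illustration only).** Inputs: n = 36 per group, two-sided alpha 0.05, 80% power (Sample size; Statistical methods). Assumption: switchers receive the full diet effect.

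- Detectable difference: √(2/36) × (1.960 + 0.842) = 0.660 SD (0.670 with the noncentral t).
- Power at uptake c: Φ(2.802 × (1 − c) − 1.960).
- c = 10%: Φ(2.521 − 1.960) = 71%.
- c = 20%: Φ(2.241 − 1.960) = 61%.
- With a Bonferroni level of 0.05/3, starting again from 80% power (0.763 SD), the values are 70% and 58%.

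These figures describe dilution of the intention-to-treat contrast. They do not measure a loss caused by the HEI rule.

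**The case against.** Adherence to an assigned diet is specific to the arm by nature, and the article never says that intake will not be compared between arms. A table of intake by arm is something an article may leave to the full protocol or analysis plan. A two-directional departure-from-baseline rule also fits the instruction that controls keep their current diet. It removes controls with a marked change whatever the reason, and for an adherent-only analysis removal is what counts. Controls are offered study-diet resources at month 24, which gives them some reason to wait. Switchers would lack the dietitian counseling, group sessions and supplements, so assuming the full effect overstates dilution.

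Much of this stands. A reader might infer that control crossovers go undetected and that separation between arms can never be shown. The documents do not support that: DHQ-III and laboratory β-hydroxybutyrate are collected without restriction by arm, and the HEI rule catches some switchers. The absence of a by-arm intake table would not be a finding on its own.

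What does not fall is the control rule, because it is stated, not merely omitted. By the article's own description HEI tracks the DGA, so the rule can retain a switcher, and it cannot separate a switcher from a permitted user of DGA materials. β-hydroxybutyrate is tied to no adherence rule, is not among the month 3 tests and says nothing about MPE uptake.

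**Conclusion.** The concern holds in a limited form. The stated rules assign each diet measure to one arm and screen controls by a non-specific HEI change, although the data for a specific check are already planned. The consequence is confined to the adherent-only sensitivity analysis and to explaining a null or positive QoL result.

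A reader might also infer that the HEI rule costs the trial power, for example a fall from 80% to 71% or 61%. That does not follow. Those values rest on assumed uptake of 10% or 20% and a full effect in switchers. They concern the intention-to-treat contrast, where keeping crossovers in their assigned arm is proper, and changing the sensitivity rule recovers none of that power. How many switchers the rule would retain is unknown, because the article gives neither an uptake rate nor the HEI change that switching would produce.

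**What to change.** 1. From DHQ-III, derive HEI, ketogenic ratio, fruit and vegetable cups and intake of the MPE-eliminated food groups in all three arms at months 0, 3, 12 and 24. Report them by arm beside the primary result.
2. In the adherent-only analysis of {20c}, keep the HEI rule and also flag and exclude controls who did not meet the TROO ketogenic-ratio rule at baseline but meet it at follow-up, or who newly meet an MPE-pattern threshold on eliminated foods. The baseline condition keeps the flag to change after randomization.
3. Fix the MPE-pattern threshold before unblinding. It must allow for the re-introduction of foods that the MPE section permits; otherwise the MPE arm itself may not match it at months 12 and 24.
4. Report how many controls each rule removes, so that HEI changers and apparent crossovers can be told apart.

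The intention-to-treat analysis stays as it is. The cost is extra scoring of questionnaires already being collected and a short addition to the sensitivity rule. The drawback is that a few more controls leave a secondary analysis on a post-randomization criterion. The article expects study activities to run until September 1, 2026, which leaves room to specify this before the data are complete.

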### Plans to promote participant retention and complete follow-up {18b}

The study team will use regular contact with study participants to identify times of stress that may result in participant dropout, and will use clearly defined protocol guidelines to allow participants to briefly modify dietary regimens and then quickly return to the study protocol to avoid attrition. Staff trained in Motivational Interviewing (MI) may have brief MI sessions to help uncover barriers that prevent participants from meeting goals. All study participants will receive retention messages from the study team which may include messages for birthdays, study anniversaries, holidays, visit and survey completion reminders, and check-ins via email, video message, and text message. Additional messages will be sent as needed to keep study participants feeling engaged and appreciated. Project Management Group (PMG) will hold weekly meetings to monitor participant engagement, proactively identify individuals at risk of dropout, and implement tailored strategies to enhance retention and ensure continued participation throughout the study. Study participants will be compensated for attending site visits and completing online surveys. $100 will be paid for months 0, 3, and 24 site visits following the completion of the study assessments and online surveys. $25 will be paid for the completion of online outcome surveys every 6 months between site visits.

### Data management {19}

Electronic data will be kept on a shared network folder managed by UIHC. The database will be password-protected with access limited to approved members of the study team. Subject data will be stored electronically in the Research Electric Data Capture (REDCap) platform [75]. Only IRB-approved research team members will have access to the REDCap data platform. Each team member will be granted access to the REDCap data system through a secure login. In the REDCap data platform, primary data is secured in the HCIS Pomerantz Data Center. Data backups are secured in the ITS Lindquist Data Center. Operating system security includes secure logins, data encryption at rest, remote system logging and configuration and change management.

### Confidentiality {27}

Each study participant’s contact information will be securely stored for internal use during the study. Study identification (ID) numbers will be used on data collection materials. Files that contain participant information will be kept in locked rooms. All electronic data will be kept on the UIHC Internal Medicine network folder. Network access will be limited to approved members of the study team. Each study team will access the folder through a secure login.

### Plans for collection, laboratory evaluation and storage of biological specimens for genetic or molecular analysis in this trial and future use {33}

Serum, plasma, and red blood cells (RBCs) will be frozen and stored for future use at the UI Tissue Procurement Core (TPC). The TPC has restricted physical access to the facilities, password-protected access control to informatics systems, encryption of data, de-identification of specimens and data, use of coded specimen identifiers. Samples will be stored in facilities with ID badge-controlled access.

### Statistical methods

#### Statistical methods for primary and secondary outcomes {20a}

Data for this study will be stored electronically using the REDCap platform at the University of Iowa and analyzed in SAS® 9.4. Baseline demographic and clinical measures collected will be summarized and tested for differences between study groups. Categorical measures are displayed as counts (percentages) and use Pearson’s chi-square or Fisher’s exact tests, depending on expected crosstab counts. Continuous measure distributions will be assessed using histograms. Normally distributed measures will be displayed as means (standard deviations) and compared using two-sample t-tests. Non-normally distributed measures will be displayed as medians (interquartile ranges) and compared using the Wilcoxon rank sum test.

The generalized linear mixed modeling (GLMM) [76] framework will be used to test the main and interacting effects of diet and time on the outcome measures of interest while accounting for repeated measures from each participant. The GLMM framework allows for non-normal distributions among the outcome measures. Other potentially important variables (age, sex, BMI, baseline smoking status, baseline alcohol use, walking assistance, years of MS, DMT use, baseline vitamin D, baseline 6-min walk distance) will be considered for inclusion in each model to assess their relationship with the outcome and to determine if they modify the estimates for the diet and time interaction. For each unique model (outcome and predictor set combination), Akaike information criterion (AIC) [77] will be obtained and utilized for model selection. Point estimates, 95% confidence intervals, and p-values of the diet mean changes in outcome measures over visits will be generated for each optimal model. For primary data analysis, data from all participants randomized at baseline will be included in an intention-to-treat analysis. A secondary per-protocol analysis will be used to examine the participants who complete the primary endpoint at 6 months for patient-reported outcomes or had clinical outcome assessments at 24 months. Hypothesis testing of the main effects in each optimal model (according to AIC) will use the Bonferroni correction for multiple comparisons between the three study treatment arms. All analyses will be conducted with two-sided tests (alpha = 0.05) using SAS software version 9.4 (SAS Institute Inc.).

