### Sample size {14}

Sample sizes required to achieve 80% power for testing between-treatment changes over time were calculated for each measure using summary statistics at baseline and 6-months from our previous randomized parallel arm trial comparing the LSF and MPE diets.

Using a group sample size of 36 and an alpha of 0.05, power and estimates for mean difference within and between groups are shown in Table 4. To ensure adequate sample size at the primary endpoint of the study, we will enroll enough participants to cover a 33% attrition rate in each group, giving a final target enrollment sample size of *n* = 54 per group.

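### The primary model's covariates are chosen by AIC after the data are seen, and three candidates that can change during follow-up are not fixed at baseline

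*Protocol article*

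**What the plan says.** All of this stands in the protocol article, Statistical methods for primary and secondary outcomes {20a}.

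- **Model.** A generalized linear mixed model with diet, time and their interaction, with repeated measures per participant.
- **Candidate covariates.** "age, sex, BMI, baseline smoking status, baseline alcohol use, walking assistance, years of MS, DMT use, baseline vitamin D, baseline 6-min walk distance". One stated purpose of considering them is "to determine if they modify the estimates for the diet and time interaction".
- **Selection.** "For each unique model (outcome and predictor set combination), Akaike information criterion (AIC) [77] will be obtained and utilized for model selection".
- **What is reported.** Estimates, 95% intervals and "p-values of the diet mean changes in outcome measures over visits will be generated for each optimal model".
- **What is tested.** "Hypothesis testing of the main effects in each optimal model (according to AIC) will use the Bonferroni correction for multiple comparisons" between the three arms, two-sided at 0.05.
- **Analysis set.** For the primary analysis, "data from all participants randomized at baseline will be included in an intention-to-treat analysis".

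The Outcomes section {12} makes change over time in the mental and physical MSQoL-54 scores the primary outcome. No separate model is named for these two scores.

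**The concern.** A confirmatory analysis should be fixed before outcomes are seen by arm. Here the covariate set is an output of the data, and the interval and p-value are then read as if that set had been chosen in advance. Three consequences follow from the text.

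- The search runs separately for each outcome, so the physical and mental scores can end up with different adjustments.
- The multiplicity correction counts arm comparisons. It does not count the model search.
- Four of the ten candidates carry the word baseline (smoking, alcohol, vitamin D, 6-minute walk). Age, sex and years of MS also lack it, but diet cannot change them. BMI, walking assistance and DMT use lack it and can change over 24 months. In a repeated-measures model they could enter as current values. Adjusting for something the diet has altered removes part of the effect being estimated. If that variable also shares causes with QoL, the adjustment can create an effect where none exists.

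**Working it through.** **1. Sample sizes used.** Sample size {14} gives 36 evaluable per group and 33% attrition: 36 / (1 − 0.33) = 53.7, rounded up to 54, and 3 × 54 = 162. This reproduces the stated enrolment. The checks below use 36 and 54 per arm. The 80% power cannot be rebuilt, because Table 4 is not shown.

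**2. Number of candidate models.** Ten covariates, each in or out: 2^10 = 1,024 main-effect sets per outcome. This is an upper figure that assumes all subsets are searched; the text names no search method.

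**3. Diet main effect, all covariates at baseline.** Simulation with three arms, one continuous follow-up outcome, no diet effect and all 1,024 sets fitted. The AIC-best model was kept, and one diet was tested against control at two-sided 0.05, with 8,000 trials per row. The covariate effects are assumptions.

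| Case | AIC-selected | All ten fixed |
|---|---|---|
| 36 per arm, covariates unrelated to outcome | 5.8% | 4.5% |
| 36 per arm, weakly prognostic (0.15 each) | 6.4% | 4.9% |
| 54 per arm, covariates unrelated to outcome | 5.4% | 4.9% |
| 54 per arm, weakly prognostic (0.15 each) | 5.7% | 4.8% |

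The Monte Carlo standard error is about √(0.05 × 0.95 / 8,000) = 0.24 percentage points. A 40,000-trial run at 36 per arm with three prognostic covariates gave 5.8% against 5.1%. The mean AIC-selected estimate stayed near zero (at most 0.004 residual SD), so there is a little excess error and no systematic bias.

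**4. Diet-by-visit change contrast, all covariates at baseline.** Write Y_it = arm + visit + arm×visit + βx_i + u_i + e_it, with the baseline visit among the responses. For a time-fixed x_i, the term βx_i cancels in Y_i2 − Y_i1. With complete, balanced data the change contrast therefore does not depend on which x_i are selected. A fitted check agrees: adding a baseline covariate left the diet-by-time estimate at 0.0569 and moved the diet main effect from −0.345 to −0.307. Simulation of this structure used five visits, a random intercept, ten baseline covariates of which three were prognostic, AIC over all subsets by maximum likelihood, and 4,000 trials per row (standard error about 0.34 points):

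| Case | AIC | No covariates | All ten fixed |
|---|---|---|---|
| 36 per arm, complete data | 4.7% | 4.8% | 4.6% |
| 36 per arm, outcome-dependent dropout | 5.1% | 5.4% | 5.0% |
| 54 per arm, dropout | 4.6% | 4.5% | 4.3% |

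No inflation is visible. Covariate-by-time terms were not assessed.

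**5. One covariate measured after randomization (illustration only).** Assume that both diets shift one covariate by 0.2 to 0.5 SD, that it shares an unmeasured cause with the outcome, and that there is no true diet effect (1,500 trials per case, one follow-up outcome). The AIC-selected model shows a spurious effect of 0.06 to 0.17 residual SD and rejects in 6.6% to 12.2% of trials. A fixed model that contains the same covariate still rejects in 5.7% to 10.9%. Most of this damage comes from the timing of the covariate, not from AIC. Fixing the model without fixing the timing would leave it in place.

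**The case against.** The strongest reply is that AIC selection over baseline covariates does almost nothing to the primary question. The primary outcome is change over time, and step 4 shows that time-fixed main effects leave that contrast essentially untouched. This stands. A reader might infer that the primary p-value is invalid, but the checks do not support that. Two limits remain: the multiplicity sentence speaks of main effects, where step 3 does find a small excess, and the cancellation needs the baseline score to be a response rather than a covariate.

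Second, nothing in the text says that BMI, walking assistance or DMT use enter as current values; other unlabelled covariates are harmless, and BMI is measured at entry for eligibility. This also stands. The bias is a possibility that the wording leaves open, in a sentence that closes it for four other variables. It is not a stated plan.

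Three further readings are tempting and go too far.

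- *Covariates are selected by how much they move the diet estimate.* The text gives this as one reason for considering them, but AIC is the only selection criterion stated. At least one of the 1,024 models was significant in 9% to 17% of null trials, but that is a ceiling for a rule the protocol does not contain.
- *AIC values will not be comparable across fits, because of the estimation method or differing records.* The article does not state the estimation method, and such detail belongs in an analysis plan.
- *Missing covariates will remove randomized participants from the intention-to-treat set.* The article does not say that such records will be dropped, and it says that missing data are modelled within the mixed model.

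It might also be said that the analysis plan can settle the covariates. However, AIC selection is a stated rule. A plan that named one fixed model would contradict the article unless the article's rule is changed.

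**Conclusion.** The point holds as a should-fix. The confirmatory model for both MSQoL-54 scores is undefined until the data are seen, the two scores may be adjusted differently, and the multiplicity correction ignores the search.

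With baseline covariates as main effects, the numerical cost is small: about 5.4% to 6.4% at nominal 5% for a diet main effect, and essentially nothing for the diet-by-visit change contrast. These figures rest on assumed covariate effects, an all-subsets search and continuous outcomes, and they exclude covariate-by-time terms.

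The more serious exposure is the unfixed timing of BMI, walking assistance and DMT use. Its size is unknown. The document gives no expected change in these variables and no link to QoL, so the figures in step 5 show only that the effect need not be trivial.

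**What to change.** - Name one primary model, the same for both MSQoL-54 scores: diet, visit, diet-by-visit, the baseline score, and a short fixed list drawn from the existing covariates. All covariates should be measured at baseline.
- Handle the baseline score either as a covariate or as a response, not both.
- Add the words *at baseline* to BMI, walking assistance and DMT use.
- Keep AIC-selected models, labelled as sensitivity or exploratory analyses.
- Record the list before the final analysis, without reference to outcomes by arm. This matters because the section on auditing trial conduct {23} has the Steering Committee meet jointly with the DSMB to review efficacy data from each arm.

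The cost is wording in the protocol and analysis plan; the sample size stays at 54 per group. The downside is that a prognostic covariate left off the list is not used in the primary model, with some possible loss of precision.

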**Methods:**

The proposed study will consist of 162 study participants attending 3 in-person site visits at months 0, 3, and 24, with online surveys every 3 months. This study will use a randomized, single-blind, controlled design to investigate the short-term (6 months) and long-term (24 months) efficacy of intervention diets on QoL and related outcomes stated above. On-site study visits will include motor, ocular and cognitive function, as well as magnetic resonance analyses. Blood and saliva biospecimens will be collected and frozen for future metabolome and microbiome analyses, respectively. Participants assigned to TROO keto and MPE diets will be given diet-specific educational materials and dietary supplements. Usual care control group will be given DGA resources and monthly educational resources. Dietary assessments will be collected by the Diet History Questionnaire III (DHQ III) at months 0, 3, 12 and 24. Registered Dietitian Nutritionists (RDNs) will deliver the dietary intervention to the TROO and MPE groups, using Social Cognitive Theory (SCT), Self-Determination Theory, and Motivational Interviewing (MI) techniques to facilitate effective behavior change.

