### Outcomes {12}

#### Primary outcome

The primary outcome of this study is changes in mental and physical QoL scores over time in the intervention groups compared to the control group assessed using the MS Quality of life 54 (MSQoL-54) questionnaire, which is a validated 54-item questionnaire of MS-specific physical- and mental health-related QoL.

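### The plan names Bonferroni for the arm comparisons; it is valid, but a step-down test with the same 5% familywise bound would give more power if both diets work

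*Protocol article*

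**What the plan says.** Statistical methods {20a} states that hypothesis testing of the main effects in each selected model "will use the Bonferroni correction for multiple comparisons between the three study treatment arms", with two-sided tests at 0.05. No step-down or closed procedure is named. The section does not say whether the family is the two diet-versus-control contrasts or all three pairs of arms.

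The primary outcome (Outcomes {12}) is "changes in mental and physical QoL scores over time in the intervention groups compared to the control group", which points to two contrasts.

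Sample size {14} opens with "Sample sizes required to achieve 80% power for testing between-treatment changes over time" and then works from this premise: "Using a group sample size of 36 and an alpha of 0.05". It does not mention the correction. Enrolment is inflated for attrition, "giving a final target enrollment sample size of *n* = 54 per group". The power entries themselves are in Table 4, which is not shown.

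**The concern.** Read plainly, Bonferroni holds every contrast to 0.05/k whatever the other contrasts show. A step-down test starts at the same threshold and relaxes it only after a rejection. It therefore never rejects less, and its familywise error stays within the same 5%.

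With three arms there is a further gain. If any two of the three pairwise equalities hold, the third holds too. Once one pair has been rejected at 0.05/3, at most one true null can remain, so the other two pairs may each be tested at 0.05 (Shaffer).

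The Discussion expects benefit on quality of life from the diets. If both work, that is where single-step Bonferroni gives up most in the chance of showing that both are effective. Recruitment has closed (Trial status), so this power cannot be recovered by enrolling more participants.

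**Working it through.** **Inputs from the protocol article**
- Evaluable per arm: 36; two-sided alpha 0.05; target power 80%; attrition 33%; enrolled per arm 54 (Sample size {14}).
- Total 162 (Abstract, Methods); correction method from {20a}.

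**Input assumed**
- Effect size, because Table 4 is not shown. I take the difference that gives 80% power with 36 per arm at 0.05: (1.96 + 0.84) × √(2/36) = 0.66 SD, or about 0.67 SD with t tests. It is set equal in both diets unless stated otherwise.

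**The plan's own figure.** 36 / (1 − 0.33) = 53.7, rounded up to 54; 3 × 54 = 162. This reproduces.

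**Power of one contrast by threshold** (normal approximation, 0.66 SD, 36 per arm)
- 0.05: 80.0%
- 0.05/2 = 0.025: 71.2%
- 0.05/3 = 0.0167: 65.8%

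**Rules compared**
- Bonferroni: reject if p ≤ 0.05/k.
- Holm, k = 2: smaller p against 0.025, then the other against 0.05.
- Holm, k = 3: 0.05/3, then 0.025, then 0.05.
- Shaffer, three pairs: smallest p against 0.05/3, then the other two against 0.05.

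**Simulation.** Three arms of 36, shared control, pooled variance (105 df), 0.67 SD in both diets, 1,000,000 trials per scenario:

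| Family | Test | Power per diet-versus-control contrast | Both diets shown |
|---|---|---|---|
| Two contrasts | Bonferroni | 71.4% | 57.6% |
| Two contrasts | Holm | 76.7% | 68.3% |
| Three pairs | Bonferroni | 65.9% | 51.0% |
| Three pairs | Holm | 69.2% | 57.6% |
| Three pairs | Shaffer | 73.7% | 66.6% |

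The gains per contrast are 76.7 − 71.4 = 5.3 points (Holm, two), 69.2 − 65.9 = 3.3 (Holm, three) and 73.7 − 65.9 = 7.8 (Shaffer, three).

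**Sensitivity of the gain per contrast**
- Equal effects of 0.5 to 0.8 SD: 3.7 to 5.5 points (Holm, two), 2.6 to 3.3 (Holm, three), 5.9 to 7.9 (Shaffer, three).
- All 54 per arm evaluable, 0.67 SD: 3.3 (Holm, two), 5.4 (Shaffer, three).
- Effects of 0.67 and 0.33 SD, Holm on two: 0.7 points for the stronger diet and 7.6 for the weaker (19.5% to 27.1%).
- Only one diet works (0.67 and 0 SD): Holm on two adds about 0.1 point; Shaffer on three still adds 7.8.
- Chance of at least one rejection in the family: unchanged, because the first step is the Bonferroni threshold (85.2% either way with two contrasts and both diets at 0.67 SD).

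**Error rates**
- Under the global null, familywise error is about 4.6% (two contrasts) and 4.4% (three pairs), the same for the step-down tests as for Bonferroni.
- With one arm far from the other two, the one remaining true null is rejected about 5.0% of the time by the step-down tests. Bonferroni tests it at 2.5% (k = 2) or 1.7% (k = 3).

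**The case against.** Bonferroni is valid and standard, and {20a} contradicts nothing by using it. That stands, and it makes this an efficiency point. A reader might infer that the plan misstates its error control or that its tests are wrong; the documents do not support this, because the familywise error stays below 5% as planned.

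The article says only Bonferroni, not single-step, and an analysis plan that is not shown could refine it. This is fair as a caution. Still, a named Bonferroni correction with no step-down version mentioned is naturally read as single-step.

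The sizes above are close to the favourable case. The 0.67 SD is assumed, and 36 per arm is the floor after attrition, whereas the primary analysis is by intention to treat with missing data handled in the mixed model. The Background also reports that an earlier, MCT-based ketogenic diet changed no clinical outcome significantly, so equal benefit of both diets is not assured. All of this stands and limits the claim.

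It is also tempting to say that Bonferroni gives nothing in return for the lost power. That goes too far. When one diet works and the other does not, Bonferroni holds the ineffective diet to a stricter rate, and it has simple simultaneous intervals that match its tests.

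Finally, {20a} attaches the correction to main effects, while the primary question concerns change over time against control. Any new wording should name the contrasts it covers.

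**Conclusion.** The point holds as a cheap improvement. With 36 evaluable per arm and 0.67 SD in both diets, Holm on the two diet-versus-control contrasts adds about 5 points of power per contrast, and Shaffer's step-down on three pairs adds about 8. The chance of showing both diets effective rises by about 11 points (68.3 − 57.6) or 16 points (66.6 − 51.0).

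A reader might take 5 to 8 points as the gain from any step-down test in any scenario. It is not: plain Holm on three pairs adds only about 3, the gains fall to about 3 (Holm, two) and 5 (Shaffer, three) with 54 per arm, and Holm on two contrasts adds almost nothing if only one diet works. The direction, that a step-down test never rejects less, needs no assumption about effect size.

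Nor does the change restore the 80% in Sample size {14}. That figure was set at an unadjusted 0.05, and a step-down test recovers only part of the difference.

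**What to change.** In {20a}, replace the Bonferroni correction with Holm's step-down procedure for the two diet-versus-control contrasts of change. If all three pairs are to stay in the family, use Shaffer's step-down instead: smallest p against 0.05/3 and, if that is rejected, the other two against 0.05.

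The cost is one sentence and a few lines of SAS code, plus some care over timing. Recruitment is complete, and efficacy data by arm are reviewed at joint meetings of the DSMB and Steering Committee (section {23}). The change should therefore be a dated amendment, justified on grounds that do not depend on the data and made before final unblinding.

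There are two downsides to disclose:
- The error rate for a single remaining true null rises from 2.5% or 1.7% to at most 5%, still within the familywise bound.
- Any result gained only by the step-down test will have a Bonferroni-adjusted interval that includes zero. If such intervals are reported, the text should say that the decision rests on the step-down p-value.
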